### Measures and data collection

All assessments will be conducted in the study school by trained research assistants, who will be blinded to group allocation at all time points (baseline, post-intervention, and 12-month follow-up). Socioeconomic information and self-report measures (S3 File) using questionnaires will occur prior to fitness assessment. Anthropometric assessments will be conducted sensitively by same-sex researcher staff when possible. The research assistants will provide a brief verbal description and demonstration of each fitness test before commencement.

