### Blinding and randomisation

Randomization will occur among schools that have been recruited and have completed baseline assessments. The schools will be matched based on the following characteristics: school area-level socioeconomic status (i.e., using Socio-Economic Class ABEP) [44]. Schools will be randomised to either a control or an intervention condition by an independent researcher using a computer-based random number generator. We will aim to recruit two classes per school (ie, one class of 8 grade and another of 9 grade) (Fig 1). Schools selected to the intervention condition will participate in the program during the study period, whereas schools allocated to the control condition will continue usual school practice.

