The introductory seminar will be designed to explain the rationale for the program and reinforce the importance of exercise for physical health (focus on muscular fitness), metabolic profile, and behavioral change such as physical activity self-monitoring and goal setting [47]. The structured PA sessions [34, 47] will follow a specifics format including i) movement-based games and dynamic stretching warm-up; ii) Resistance training skill development; iii) high-intensity workout, and iv) cool-down. Participants will be able to select from a variety of predesigned circuit cards, which will be released across the program to promote variety and sustain participant interest. The level of intensity for each session component will be guided by Borg´s CR-10 rating of perceived exertion scale.

To promote exercise adherence, sessions will be developed with a focus on enhancing students’ autonomous motivation [34, 47], within and beyond the school setting by satisfying their basic psychological needs for autonomy (feeling in control), competence (feeling capable), and relatedness (feeling connected with others) [46]. Teachers will learn to facilitate sessions using the Supportive, Active, Autonomous, Fair, and Enjoyable (SAAFE) teaching principles [48], which will serve as a framework for the design and delivery of the physical activity sessions, as well as session observations. They will be educated about the importance of and provided with strategies for, integrating SAAFE principles in their lessons during the professional learning workshop.

Participants’ need for autonomy will be satisfied by the teacher-delivery seminar and providing opportunities for choice within sessions (e.g., type of activity and preferred music playing). Competence will be satisfied using positive and specific feedback from teachers to enhance self-efficacy (e.g., providing encouragement, giving specific feedback on technique, modeling correct performance) [47]. Teachers will be encouraged to adopt practices that support relatedness and group cohesion during the sessions (i.e., encouraging supportive behavior among students) [48]. Several precautions will be undertaken to ensure the safety of participants including 1) explanation of correct technique for all exercises at the beginning of the program, whilst students are learning the techniques; 2) inclusion of warm-ups and cool-downs, and 3) reminders for teachers and research staff member to monitor and correct exercise technique.

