Provision of teacher handbook, fitness equipment, and session resources, provided by the research team	Once	Schools will be provided facilitator handbooks, sets of circuit cards and fitness equipment packs.
Interactive seminar	1×1 hour seminar	Students will participate in an interactive seminar by a member of the research team. The interactive seminar will provide important information about the programme components and behavioural messages (including current recommendations for youth physical activity, healthy eating, screen-time). It will also address relevant information on physical, metabolic and mental health.
Structured physical activity program	2/week	The session will include bodyweight and elastic tubing resistance training, aerobic-based and strength-based activities, and high-intensity fitness challenges that will be run at school during physical education lessons for 16 weeks (2 times per week). Each exercise session will last approximately 20 min. Students will be able to select from a variety of pre-designed cards incorporating both aerobic-based and resistance-based exercises. Behavioural messages (i.e., be physically active, limit screen time, foods, and sugar-sweetened beverages) will be reinforced at the end of sessions (e.g., cooldown).
Pedometer plus goals setting	16-week	The pedometer plus goals setting will be used as a strategy to promote participation in PA of adolescents (out of school). Participants will wear Yamax SW700 pedometers for physical activity self-monitoring and will receive a new goal-setting (based on the number of steps measured in the baseline week) to achieve weekly. The goals setting will be progressive and changed every two weeks, and this strategy has as its objective propose a realistic goal setting aim to achieve at least 10000–11700 steps/day.
e-health	Twice per week	Adolescents of the intervention group will receive messages about healthy behavior (i.e, active lifestyle and healthy eating) by WhatsApp®.
Parental involvement	Once per week	Parents of intervention group students will receive weekly messages about the benefits of physical activity and healthy eating by WhatsApp® to support their adolescent’s healthy behavior change at home.

Adapted by Resistance Training for Teens program [34]–RT: Resistance training; IG: intervention group.

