#### Cardiorespiratory fitness

Will be assessed using the PACER FITNESSGRAM test and will be administered following standardized procedures [56], which have excellent validity and reliability in this population [57]. Test administrators will provide verbal encouragement during the shuttle to maximize participant motivation. A 20m course will be set up on a hard surface with participants instructed to run back and forth between two sets of lines while keeping pace with a pre-recorded cadence (indicated by a single beep for each 20m shuttle). The test begins at 8.5km/h (slow pace), and increases by 0.5km/hour with each passing minute. The test will be terminated when the participants fail to complete two consecutive laps in the allotted time or voluntarily dropped out due to fatigue. The last successful stage will be recorded and converted into the number of 20m laps completed, and the total number of laps will be used to estimate maximal aerobic capacity (VO_2max_) using the equation: 45.619+(0.353*PACER laps)–(1.121*age) [58].

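### Assessor blinding is claimed at all three time points, but with whole schools allocated and all testing done in the school it is automatic at baseline and not assured at either follow-up.

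*Protocol article*

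**What the plan says.** Measures and data collection states: "All assessments will be conducted in the study school by trained research assistants, who will be blinded to group allocation at all time points". It then lists the time points as baseline, post-intervention and 12-month follow-up. The statement carries no qualification.

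Blinding and randomisation sets the unit and timing of allocation: "Schools will be randomised to either a control or an intervention condition by an independent researcher using a computer-based random number generator", and "Randomization will occur among schools that have been recruited and have completed baseline assessments". It also says "We will aim to recruit two classes per school (ie, one class of 8 grade and another of 9 grade"). Sample size calculation uses 29 participating students per class, three classes per school and a total of 174 students. The abstract gives about 140.

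On delivery, Table 1 under Intervention says "Schools will be provided facilitator handbooks, sets of circuit cards and fitness equipment packs". It also describes twice-weekly sessions in physical education lessons, pedometers with step goals and WhatsApp messages. Research staff attend the programme workshop (Table 1), and the safety precautions under Intervention include "reminders for teachers and research staff member to monitor and correct exercise technique".

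On testing, Cardiorespiratory fitness says of the PACER run: "Test administrators will provide verbal encouragement during the shuttle to maximize participant motivation". Muscular fitness says the push-up test ends when the required angle, the metronome pace or back position is not kept, or when the participant can do no more. The assessor calls out the warnings.

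**The concern.** A blinding statement tells the reader that knowledge of the arm could not have influenced the measurements. Here it covers three time points with equal confidence, although allocation does not exist at the first and is shared by a whole school at the other two. When the assessor works inside the school, the arm of every pupil tested there can become known at once. Pupils know what they took part in and talk to the assessor during testing.

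This matters where assessor conduct can move the score. Warmer encouragement in PACER, or more lenient calls on push-up form, in schools known to have had the programme would look like a fitness gain. Muscular and cardiorespiratory fitness are named secondary outcomes and part of the stated hypothesis. A difference in conduct between schools would act on the whole school, so testing more pupils in the same schools would not average it out.

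**Working it through.** The article gives no figure to reproduce. The check compares its sections and adds one piece of arithmetic on the number of schools.

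**Step 1. When the claim has content.** Schools are allocated only after baseline testing is complete. At baseline there is no allocation to know, so blinding holds by construction. The claim does work only at 24 weeks and at 12 months (48 weeks).

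**Step 2. How many schools.** The text does not state the number of schools, and Figure 1 is not shown in the copy reviewed. It can be implied from:

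schools = total students / (classes per school × students per class)

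- Two classes per school (Blinding and randomisation), total 174: 174 / (2 × 29) = 174 / 58 = 3.0.
- Three classes per school (Sample size calculation), total 174: 174 / (3 × 29) = 174 / 87 = 2.0, or one school per arm.
- Two classes per school, abstract total of about 140: 140 / 58 = 2.4.

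The inputs therefore point to about two or three schools, all public schools in one city. This assumes that the stated class size is achieved. Smaller participating classes would mean more schools.

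**Step 3. What one disclosure reveals.** If individual pupils were randomised within a school, one remark would unmask one pupil. Here it unmasks every pupil tested at that school. On the figures above that is about 58 pupils with two classes (2 × 29) or 87 with three (3 × 29), before dropout. With two or three schools, a difference in assessor conduct between schools is also largely inseparable from the difference between arms.

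**Step 4. Which outcomes are exposed.**

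| Outcome | Route for assessor influence in the text |
|---|---|
| Accelerometer activity (primary) | Not assessor-judged |
| Blood markers | Laboratory assay; not assessor-judged |
| PACER | Verbal encouragement; test can also end on voluntary withdrawal |
| Push-ups | Ended partly on judged angle and technique |
| Sit-to-stand | Timed 30-second count; less judgement than push-ups |
| Questionnaires | Self-reported by pupils, for whom no blinding is claimed |

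The exposure is chiefly PACER and push-ups.

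**Step 5. Whether a size can be given.** The article's equation converts each PACER lap to 0.353 units of estimated maximal aerobic capacity. It does not say how many laps a difference in encouragement would produce, and nothing else in the article does. No estimate of bias follows.

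**The case against.** A reader might infer that follow-up blinding cannot hold, so that the fitness outcomes are in effect open-label. The documents do not support that. An independent researcher performs the allocation, and nothing says that assessors are told it. Outside assessors who do not know a school's arm could stay masked, at least in part. A 15-minute staff presentation leaves nothing for a later visitor to see, nothing says that cards or equipment are on display during testing, and the last visit is months after the programme ends. Disclosure is a risk, not a certainty.

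A reader might also infer that delivery staff will act as assessors. The text does not say so. It uses different labels for the two roles, and a requirement that assessors be blinded already implies that someone who has supported sessions should not test. This stands, and the roster rule in the fix only makes that implication explicit.

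The tests are also more bounded than they might seem. PACER follows standardised procedures with a recorded cadence and a fixed stopping rule. Push-ups are paced by a metronome with written criteria, and no encouragement is described for them. This narrows the room for bias but leaves the encouragement in PACER and the judgement of form in push-ups.

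Finally, non-disclosure instructions and blinding checks may sit in the full protocol, and their absence from a journal article is no finding. That is accepted. What remains is what the article does state: an unqualified claim at follow-up that its own allocation and testing arrangements make hard to keep.

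**Conclusion.** The point holds in a limited form. Assessor blinding is automatic at baseline and not assured at 24 weeks or 12 months, because schools are the unit of allocation, testing is done in the school, and the stated inputs imply about two or three schools. The consequence is limited to secondary fitness outcomes, mainly PACER and push-ups. The primary outcome and the laboratory values are not affected by this route.

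The conclusion rests on two assumptions: that the class sizes and totals in the article describe the schools actually recruited, and that pupils or surroundings may give the allocation away. The direction and size of any bias are unknown. The change is worth making because it is cheap and the route to bias is real, but it does not undermine the trial's main comparison.

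**What to change.** 1. In Measures and data collection, replace the unqualified statement with one to this effect: assessors are blinded at baseline, which precedes randomisation; masking will be attempted at 24 and 48 weeks but is not assured, because allocation is by school.
2. In the same place, state that staff who attended the programme workshop, supported sessions or ran the messaging will not conduct follow-up fitness tests.
3. In Cardiorespiratory fitness, specify one standard encouragement script for PACER, used in every school and at every time point.
4. Interpret and report PACER and push-up results with this limit in mind, and say that the accelerometer and laboratory outcomes are not assessor-judged.

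The cost is a less favourable stated property, slightly less freedom in rostering staff, and a short script. Sample size, visit schedule and intervention are unchanged.

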### Primary outcome

#### Physical activity

Adolescents will be instructed to wear an Actigraph GT3X accelerometer on the hip at the height of the anterior iliac spine for all days (except when bathing, swimming, sleeping) for seven consecutive days. The subjects who use at least a wear time of >8 h on three days or more (including one weekend) will be included in the valid analyses data. The time (minutes/day) spent in physical activity of different light, moderate and vigorous intensities will be estimated, using validated cut-off points [52]. Non-wear time, defined as ≥60 min of continuous ‘0’ counts, will be removed from the data set [53]. Weekday and weekend days physical activity will be calculated separately (i.e., mean minutes per day).

### Secondary outcomes

#### Muscular fitness

Upper body muscular and lower body muscular endurance will be assessed using a 90-degree push-up [54] and sit-to-stand test [55], respectively. In the 90-degree push-up test, the participant should lower their body until a 90-degree angle is formed at the elbow before pushing back up, using a cadence of 40 beats per minute. The test will be concluded when the participant either fails to do a push-up in the angle required on two non-consecutive repetitions (warning verbalised by an assessor, repetitions counted), fails to maintain movement in time with the metronome, fails to maintain appropriate technique (back straight) or on the volitional failure of the test. To assess lower body muscular endurance, participants will sit in a chair (regardless of the height of the participant) with his/her back against the back of the chair. The students will be asked to go from a sitting to a standing position and back to a sitting position for 30 seconds as many times as possible.

#### Cardiorespiratory fitness

Will be assessed using the PACER FITNESSGRAM test and will be administered following standardized procedures [56], which have excellent validity and reliability in this population [57]. Test administrators will provide verbal encouragement during the shuttle to maximize participant motivation. A 20m course will be set up on a hard surface with participants instructed to run back and forth between two sets of lines while keeping pace with a pre-recorded cadence (indicated by a single beep for each 20m shuttle). The test begins at 8.5km/h (slow pace), and increases by 0.5km/hour with each passing minute. The test will be terminated when the participants fail to complete two consecutive laps in the allotted time or voluntarily dropped out due to fatigue. The last successful stage will be recorded and converted into the number of 20m laps completed, and the total number of laps will be used to estimate maximal aerobic capacity (VO_2max_) using the equation: 45.619+(0.353*PACER laps)–(1.121*age) [58].

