## Abstract

This trial aims to investigate the effects of the ActTeens physical activity program, on adolescents’ physical activity level, health-related fitness, cardiometabolic and mental health. The trial will aim to recruit ~140 adolescents (aged 13–14 years). Participants will be randomized into either intervention or control groups. The intervention will be guided by social cognitive theory and self-determination theory and implemented over one school term (24-weeks). The *ActTeens Program* will include: (1) structured physical activity sessions delivered within physical education, including movement-based games and dynamic stretching warm-ups; resistance training skill development; high-intensity training workouts; and cool-downs; (2) self-monitoring plus goal setting for physical activity by pedometer-smart wearable; and (3) healthy lifestyle guidance (social support) by WhatsApp® messages about healthy eating and regular physical activity for the intervention and parents groups. Study outcomes will be assessed at baseline, 24-weeks from baseline, and 12-months from baseline. Physical activity (accelerometer) is the primary outcome. Secondary outcomes include muscular and cardiorespiratory fitness, cardiometabolic profile, and mental health. A process evaluation will be conducted (i.e., recruitment, retention, attendance, and program satisfaction). This project will have the potential to address many questions and debates regarding the implementation of physical activity interventions in low-and- middle-income countries.

**Trial registration:** ClinicalTrials.gov NCT05070377. Registered on 7 October 2021.

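### PACER result is recorded as a stage and converted to laps, but a stage number alone cannot give the lap count that the VO2max equation needs

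*Protocol article*

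**What the plan says.** All of the scoring text is in the protocol article, under Cardiorespiratory fitness.

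- Recorded item: "The last successful stage will be recorded and converted into the number of 20m laps completed".
- Quantity used: "the total number of laps will be used to estimate maximal aerobic capacity", through the equation "45.619+(0.353*PACER laps)–(1.121*age"), so each lap is worth 0.353 units.
- Speeds: "The test begins at 8.5km/h (slow pace), and increases by 0.5km/hour with each passing minute". The cadence is "indicated by a single beep for each 20m shuttle".
- Stopping rule: the test ends when students "fail to complete two consecutive laps in the allotted time or voluntarily dropped out due to fatigue".
- Conduct: the test "will be administered following standardized procedures", with a citation.

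The section does not define a stage. It also does not say whether laps run in a stage that the student does not finish are added or dropped. The Abstract places cardiorespiratory fitness among the secondary outcomes: "Secondary outcomes include muscular and cardiorespiratory fitness, cardiometabolic profile, and mental health". Study objectives names it in the second aim.

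**The concern.** The equation takes laps, but the item named as recorded is a stage, and laps are to be derived from it. A stage lasts a minute and contains several laps, so everyone who stops within the same unfinished stage would get the same score. The stopping rule works lap by lap, so assessors already follow individual laps and the exact count is there to be written down.

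On the literal reading the stakes are these:

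- absolute VO2max is too low at every visit;
- rounding error enters at both baseline and follow-up, which makes the estimated group difference less precise;
- because the wording is open, assessors could score unfinished stages differently between schools or visits.

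**Working it through.** The article states no lap count, lap SD or power figure for PACER, so there is no stated result to reproduce. The check has three steps.

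**1. Laps per stage, from the stated speeds.** Laps in a one-minute stage = speed (km/h) × 1000 / 60 / 20. For stage 1, 8.5 × 1000 / 60 / 20 = 7.08. If only finished stages count, the largest possible loss is the whole laps in the unfinished stage minus 1. The VO2max loss is 0.353 times that.

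| Stage | km/h | Laps | Whole laps | Cumulative | Largest loss (laps) | Largest loss (VO2max) |
|---|---|---|---|---|---|---|
| 1 | 8.5 | 7.08 | 7 | 7 | 6 | 2.12 |
| 2 | 9.0 | 7.50 | 8 | 15 | 7 | 2.47 |
| 3 | 9.5 | 7.92 | 8 | 23 | 7 | 2.47 |
| 4 | 10.0 | 8.33 | 8 | 31 | 7 | 2.47 |
| 5 | 10.5 | 8.75 | 9 | 40 | 8 | 2.82 |
| 6 | 11.0 | 9.17 | 9 | 49 | 8 | 2.82 |
| 7 | 11.5 | 9.58 | 10 | 59 | 9 | 3.18 |
| 8 | 12.0 | 10.00 | 10 | 69 | 9 | 3.18 |
| 9 | 12.5 | 10.42 | 10 | 79 | 9 | 3.18 |

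The ceiling therefore runs from 6 to 9 laps. Nine is reached only by a student who has passed 49 laps and then stops one lap short of finishing a stage.

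**2. Typical loss.** If the stopping point is uniform within a stage of L laps, the mean loss is (L − 1)/2 and the error SD is √((L² − 1)/12). For L = 8 these are 3.5 laps and √(63/12) = 2.29 laps. A student who improves by 3 laps stays in the same stage with probability (L − 3)/L, which is 4/7 = 57% for L = 7 and 7/10 = 70% for L = 10. Most such students would show no change, and the rest would jump by a whole stage.

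**3. Effect on the comparison.** This was simulated with 1,000,000 pairs per scenario. Baseline and follow-up laps were bivariate normal, rounded, cut off at zero and floored to the last finished stage. Means, SDs and correlations are assumptions. The residual variance ratio is the baseline-adjusted variance with floored scores divided by that with true laps.

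| Mean, SD (laps) | Mean loss (laps; VO2max) | Lose ≥ 9 laps | Ratio, r = 0.60 | r = 0.75 | r = 0.85 | r = 0.90 |
|---|---|---|---|---|---|---|
| 25, 12 | 3.5; 1.24 | 0.1% | 1.02 | 1.07 | 1.17 | 1.29 |
| 30, 12 | 3.7; 1.30 | 0.2% | 1.03 | 1.09 | 1.19 | 1.32 |
| 30, 15 | 3.6; 1.28 | 0.6% | 0.99 | 1.03 | 1.10 | 1.18 |
| 40, 18 | 3.9; 1.37 | 2.4% | 0.99 | 1.02 | 1.07 | 1.14 |

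Ratios just under 1 mean no loss: flooring also shrinks the spread of scores slightly. Confidence interval width follows the square root of the ratio, so 1.17 means about 8% wider and 1.32 about 15% wider. In these scenarios a true shift of 3 laps in one arm appears as about 2.85 to 2.9 laps.

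**The case against.** The strongest reply is that no loss is stated. The section speaks of laps completed and of total laps, stops the test by a lap-level rule, and defers administration to a cited standard procedure. A record of stage plus shuttle reached, converted to total laps, would fit the sentence and lose nothing. A journal article may also leave the score sheet to the full protocol. This stands to the extent that a reader might infer that the trial will certainly discard up to 9 laps per student, and the text does not establish that. It does not dispose of the point. The only recorded item the section names is the stage, laps are described as derived from it, and that derivation cannot be done exactly. This is a scoring rule that the article does state, and states inadequately.

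A second reply is that the effect on the trial's conclusions is small. That also stands. One rule applies to both arms, and Measures and data collection says that assessors are blinded. A reader might infer a biased treatment effect, but the downward shift largely cancels in the between-group difference. The upper end of the precision loss needs a high baseline correlation and a small SD. At a correlation of 0.60 the loss is about 0 to 3%.

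A cross-sectional comparison makes the cost look smaller still, because floored and true laps correlate at 0.97 to 0.99. That is not the relevant measure here. Statistical analyses plans to analyse change from baseline, which removes much of the stable difference between students and leaves rounding error from both visits.

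**Conclusion.** The point holds as a minor one. The recording rule as written does not supply the quantity that the equation needs. On the literal reading:

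- the average loss is about 3.5 to 4 laps, or 1.2 to 1.4 VO2max units;
- the ceiling is 6 to 9 laps across stages 1 to 9, and a 9-lap loss is rare (well under 1% of students at assumed means of 25 to 30 and SDs of 12 to 15);
- baseline-adjusted residual variance rises by about 0 to 30%, for an assumed SD of 12 to 18 and correlation of 0.60 to 0.90;
- bias in the between-group difference is small.

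The laps per stage and the ceilings follow from the article's own speeds. The average loss and the variance figures rest on assumed lap distributions and correlations. If assessors in fact log the shuttle reached within each stage, nothing is lost and only the wording needs correcting. The primary outcome, accelerometer physical activity, is not affected.

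**What to change.** Under Cardiorespiratory fitness, replace the recording sentence with one stating that the total number of 20 m laps completed is counted and recorded for each student at each visit, including laps run in an unfinished stage, and that this count enters the VO2max equation. Delete the stage-to-laps conversion and make the score sheet match. This costs one line in the test procedure. It needs no extra staff or testing time, because the stopping rule already requires laps to be followed one by one. If data have already been collected as stages only, say so when the outcome is reported and note that absolute VO2max is understated.
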